### Ethics approval and consent to participate

The study strictly follows protocols regarding informed consent forms, confidentiality, and anonymity. An informed consent form with guidelines, project objectives, and a description of procedures, possible risks, and benefits will be provided. Participants will also be informed that participation is voluntary and that they can withdraw from the study at any time. This study will be conducted in accordance with the Declaration of Helsinki and was approved by the facility’s institutional review board on February 7, 2023 (approval number: 38626420.6.0000.5347) and registered in the Clinical Trials Database (NCT05847075). All files containing the participants’ data will be stored in a secure password-protected databasethat will be accessed only by authorized members of the research team.

### Allocation

Participants will be randomly assigned to groups according to a sequence of computer-generated random numbers. This sequence will be obtained in Microsoft Excel (Redmond, Washington, United States) in a 1:1 ratio, with blocks of eight or six participants to complete the total number calculated. A sealed envelope containing the allocation code will be opened at the beginning of the treatment in the presence of the participant according to the order of entry into the study.

Owing to the nature of the interventions, the researcher conducting the exercise sessions and participants will not be blinded. To ensure assessor masking, the participants will be asked to omit their assigned groups and not talk about their interventions during the outcome evaluation sessions. In case of unintentional unblinding for any reason, the researcher will notify the principal researcher.

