## OBJECTIVE

Due to few well-conducted clinical trials, we will perform a randomized, three arm, double-blind, parallel study, aiming to compare the properties of resistance training (RT) and HT in type 2 diabetes mellitus (T2DM). We hypothesize that RT and HT will reduce HbA1c levels, improve metabolic and inflammatory profiles, and attenuate gut dysbiosis and the HSR.

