### Interventions

Volunteers who met the inclusion criteria will be guided through the study and asked to sign a written informed consent form before enrollment in the trial. The participants will be randomized into the following intervention groups: control, RT or HT. In the control group, participants will not receive any intervention. In the intervention group RT, participants will perform supervised exercises in a gymnasium on three non-consecutive days of the week for a total of 12 weeks. Each session will last approximately 60 min and consist of warm-up, resistance training, and cool-down. All sessions will be conducted by qualified sports and exercise scientists.

The RT program will consist of a combination of upper- and lower-body exercises using gymnasium equipment, free weights, and body weight (functional exercises) as the primary resistance. The 12 weeks RT will be divided into three mesocycles of four weeks each (please see details of sets, repetitions, and intervals in Table 1). The exercises will include leg press, knee extension, leg curl, biceps curl, triceps extension, lat pulldown, shoulder press, bench press, and abdominal crunch exercises. Before the start of the training period, the participants completed a familiarization session to practice the exercises they would perform further during the training program when the exercise load was individually tested. Resistance training was performed using two–three sets per exercise at intensities between 12 and 15 maximum repetitions (the heaviest possible weight to perform 12–15 repetitions), as shown in Table 1. The intensity of the functional exercises was controlled using the OMNI scale,^
21
^ with each session lasting 60 min.

**Table 1 T1:** Resistance training program

Mesocycle	Weeks	Repetitions/load	Number of sets	Interval between sets
**1**	1–4	12/15	2	1 min
**2**	5–8	12/15	3	1 min
**3**	9–12	10/12	3	1 min and 30 s

Participants in the HT group will undertake whole body heat treatment according to previous methods.^
22

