### Statistical considerations

To assess the effect of exercise on plasma HSP levels between the groups post-intervention, we assumed 80% power, 5% significance level, and an effect size (Cohen’s F) of 0.4. We estimated a dropout rate of 10%, and the calculated total number of patients was 22 in each group.^
24
^

The randomly assigned participants’ data will be analyzed according to the intention-to-treat principle as the primary choice and the per-protocol principle, with treatment, time, and treatment-time interaction registered as fixed effects. We will qualitatively document the reasons for, and details of, each withdrawal case. The normality of the data will be tested using the Shapiro-Wilk test. Mean and standard deviation will be used to describe parametric continuous variables, with median and interquartile range for non-parametric variables, and absolute and relative frequencies for categorical variables. Analysis of variance (ANOVA) will be used to compare the final outcomes. Treatment effects (group, time, and group interaction) will be estimated using Generalized Estimation Equations (GEE), followed by the Bonferroni post-hoc test (P < 0.05). Multiple linear regression analysis (backward method) will be performed to investigate the impact of routine pharmacotherapy, sex, and age on the primary and secondary outcomes. SPSS Professional software (version 20.0; IBM Corp., Armonk, New York, United States) will be used for all analyses.

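### The stated 1:1 ratio with blocks of eight or six does not fit three arms: a block of eight cannot be split equally, so 22 per arm is not guaranteed (minor correction)

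*Protocol article*

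**What the plan says.** The Objective section describes the design: "we will perform a randomized, three arm, double-blind, parallel study". The Interventions section names the arms: "The participants will be randomized into the following intervention groups: control, RT or HT". Statistical considerations sets equal group sizes: "the calculated total number of patients was 22 in each group". With three groups that is 3 × 22 = 66.

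The Allocation section gives the rule for building the list, a computer-generated random sequence made in a spreadsheet: "in a 1:1 ratio, with blocks of eight or six participants to complete the total number calculated". The article states no unequal ratio, no composition for a block of eight, and no rule for compensating between blocks.

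**The concern.** A permuted block holds equal allocation only if its size is a multiple of the number of arms. A ratio of 1:1 with blocks of eight and six would fit two arms, where the blocks are 4:4 and 3:3. Over three arms, six still works and eight does not. Whoever builds the list must therefore either drop the blocks of eight or invent a composition for them, and a reader cannot tell which was done.

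Two things are at stake. One is the planned balance of 22 per arm, with a small cost in precision if it is missed. The other is that sequence generation should be reproducible from its description. The article could have left block sizes to the full protocol. It states them, and what it states does not fit its own number of arms.

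**Working it through.** **Inputs.** Arms: 3 (Objective; Interventions). Block sizes: 8 or 6 (Allocation). Planned size: 22 per arm, 66 in total (Statistical considerations).

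**The plan's figure.** A one-way ANOVA with three groups, Cohen's f = 0.4 and two-sided 5% level (noncentral F, λ = f² × N) needs 22 per group for at least 80% power; at N = 66 the power is 81.8%. So 22 per group is a three-arm figure. It is reproduced before any allowance for dropout. Whether it includes the stated 10% is a separate question and does not affect this point, which rests on divisibility.

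**Step 1, divisibility.**
- 6 / 3 = 2, so a block of six is 2:2:2.
- 8 / 3 = 2.67, remainder 2, so the closest split of a block of eight is 3:3:2.

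**Step 2, ways to reach 66 with complete blocks.** Solve 8a + 6b = 66, where a is the number of blocks of eight and b the number of blocks of six. The only non-negative solutions are:
- a = 0, b = 11
- a = 3, b = 7
- a = 6, b = 3

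Only the first, with no block of eight, is balanced in every block: 11 × 2 = 22 per arm.

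**Step 3, arm totals when blocks of eight are split 3:3:2.** Each arm starts from 2b + 3a and loses one for each block of eight in which it is the short arm.

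*Three blocks of eight, seven of six.* The start is 14 + 9 = 23 per arm. With the short arm chosen at random there are 3³ = 27 equally likely patterns:

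| Short-arm pattern | Patterns | Share | Totals |
|---|---|---|---|
| Each arm short once | 6 | 22% | 22/22/22 |
| One arm twice, one once | 18 | 67% | 21/22/23 |
| Same arm three times | 3 | 11% | 20/23/23 |

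*Six blocks of eight, three of six.* The start is 6 + 18 = 24 per arm, with 3⁶ = 729 patterns. Exactly 22/22/22 needs each arm to be short twice: 90 / 729 = 12%. The extreme, 24/24/18, occurs in 3 / 729 = 0.4%.

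*Same arm short by construction.* Totals are 23/23/20 with three blocks of eight and 24/24/18 with six.

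**Step 4, cost in precision.** The variance of a difference between two arm means is proportional to 1/n₁ + 1/n₂.

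| Arms compared | 1/n₁ + 1/n₂ | Change in variance from 22 v 22 |
|---|---|---|
| 22 v 22 | 0.0909 | reference |
| 21 v 23 | 0.0911 | +0.2% |
| 21 v 22 | 0.0931 | +2.4% |
| 20 v 23 | 0.0935 | +2.8% |
| 18 v 24 | 0.0972 | +6.9% |

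In standard error, 20 v 23 costs about 1.4% and 18 v 24 about 3.4%. The contrast between the two larger arms gains a little precision in each case.

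**The case against.** The strongest case on the other side has four parts.

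*Equal totals are still reachable.* Eleven blocks of six give 22/22/22, and so do three or six blocks of eight if the short arm is rotated. This stands. A reader might infer that equal arms cannot be produced at all, but the documents do not support that. What is impossible is balance inside a block of eight. What is missing from a list that uses such blocks is a guarantee of balance overall.

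*1:1 may be loose shorthand for equal allocation.* It may, and on that part the defect is only notation. The block of eight fails on either reading. A reader might also take 1:1 literally, as 4:4 with one arm absent from the block, and conclude that arm is confounded with calendar time. The Interventions section randomises to all three arms, so that reading contradicts the article. A randomised 3:3:2 block keeps all three arms present throughout, and no confounding with time is shown.

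*The large imbalances rest on an assumption.* Totals of 23/23/20 and 24/24/18 need the same arm to be short in every block of eight. Nothing in the article says so, and the sequence is described as random. These totals are an upper limit, not an expectation.

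*This is a condensed article.* The full protocol may give the composition of each block. That would excuse silence on the composition. It does not make the stated combination of ratio, block sizes and three arms consistent.

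**Conclusion.** The allocation rule as printed does not fit a three-arm trial. Any list that contains blocks of eight departs from equal allocation within those blocks and does not guarantee 22 per arm; a list of blocks of six alone does both.

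The expected effect is small: with three blocks of eight and a random short arm, arms differ by at most three patients and no pairwise variance rises by more than about 3%. The limit, with six blocks of eight and one arm always short, is a gap of six patients and a 6.9% rise in variance for the contrasts with that arm.

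These figures assume that the list ends on a complete block at 66, that each block of eight is split 3:3:2, and that the short arm is either random or fixed as stated. The article confirms none of these. The finding supports no claim of bias or of damage to the primary comparison. It is a minor correction, worth making because sequence generation should be reproducible from its description.

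**What to change.** State the ratio as 1:1:1 and use only block sizes divisible by three. Two options reach the planned total exactly:
- Blocks of six only: 11 × 6 = 66, with 11 × 2 = 22 per arm.
- Blocks of six and nine in random order: 5 × 6 + 4 × 9 = 66, with 5 × 2 + 4 × 3 = 22 per arm. This keeps a varying block size, as the article's wording appears to intend.

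Apply this only to a part of the list not yet generated or used. The section on recruitment and participant timeline gives January 2024 to December 2025, so allocation may be under way or complete. If it has begun, keep the assignments already made and report the block sizes actually used, with the composition of any block of eight.

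The cost is one corrected sentence and, where part of the list is still open, generating that part again.

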### Interventions

Volunteers who met the inclusion criteria will be guided through the study and asked to sign a written informed consent form before enrollment in the trial. The participants will be randomized into the following intervention groups: control, RT or HT. In the control group, participants will not receive any intervention. In the intervention group RT, participants will perform supervised exercises in a gymnasium on three non-consecutive days of the week for a total of 12 weeks. Each session will last approximately 60 min and consist of warm-up, resistance training, and cool-down. All sessions will be conducted by qualified sports and exercise scientists.

The RT program will consist of a combination of upper- and lower-body exercises using gymnasium equipment, free weights, and body weight (functional exercises) as the primary resistance. The 12 weeks RT will be divided into three mesocycles of four weeks each (please see details of sets, repetitions, and intervals in Table 1). The exercises will include leg press, knee extension, leg curl, biceps curl, triceps extension, lat pulldown, shoulder press, bench press, and abdominal crunch exercises. Before the start of the training period, the participants completed a familiarization session to practice the exercises they would perform further during the training program when the exercise load was individually tested. Resistance training was performed using two–three sets per exercise at intensities between 12 and 15 maximum repetitions (the heaviest possible weight to perform 12–15 repetitions), as shown in Table 1. The intensity of the functional exercises was controlled using the OMNI scale,^
21
^ with each session lasting 60 min.

**Table 1 T1:** Resistance training program

Mesocycle	Weeks	Repetitions/load	Number of sets	Interval between sets
**1**	1–4	12/15	2	1 min
**2**	5–8	12/15	3	1 min
**3**	9–12	10/12	3	1 min and 30 s

Participants in the HT group will undertake whole body heat treatment according to previous methods.^
22
^ Participants will be housed in an environmental chamber initially set at 55.0°C on three non-consecutive days of the week. Each session will last 60 min. During the sessions, the rectal temperature, heart rate (HR), blood pressure, and heat discomfort will be constantly measured. According to pilot testing, this protocol induces an approximate 1.2°C raise in the individual’s core temperature and remains increased after the session for an additional 15 min, before it starts to drop (Figure 1a). The HR increases and blood pressure, particularly diastolic pressure, decreases during the session (Figure 1b and Figure 1c, respectively). The core temperature initially decreases (10-15 minutes after the beginning), probably owing to rapid skin vasodilation and a blood flow shift from the center to the periphery. After approximately 20 min in the chamber, the core temperature starts to rise, as expected. The characteristics of the participants from the preliminary study are shown in Table 2.

### Body temperature assessment and thermal sensation

To measure the rectal temperature, a flexible thermometer (RET-1 Physitemp Instruments, Clifton, New Jersey, United States of America) will be inserted 10-12 cm beyond the anal sphincter (self-inserted by the participant following the researcher’s instructions). Skin thermometers will measure the skin temperature on the upper back, arm, and leg (left hemibody) (SST1, Physitemp). The environmental chamber will be set at 55.0°C. Participants’ temperatures will be continuously monitored and recorded every 5 min throughout the session. If a participant reaches a rectal temperature > 39.0°C and presents symptoms such as nausea, disorientation, tiredness, abdominal pain, or headache, the session will be stopped. In addition to temperature measurements, a perceptual scale was used to identify thermal sensation and thermal comfort. To this end, participants will be asked about their thermal sensation (9-point scale from “very cold” to “very hot”) and thermal comfort (6-point scale from “very comfortable” to “very uncomfortable”) every 10 min during the session.^
23
^

### Strategies for trial retention

Participants will be asked to monitor adverse events once a week during face-to-face visits. Moreover, phone calls or text messages will be used to remind participants of their scheduled or missed visits.

### Study outcomes

Outcomes will be evaluated at baseline and at the end of the study (12^th^ week). Outcome assessors and data analysts will be blinded to the intervention assignments. The primary outcome will be HSR.

A set of secondary clinical outcomes will include: Body composition and physical fitness (anthropometric measurements, anthropometric and visceral adipose tissue measurements, dual-energy X-ray absorptiometry scan, peak VO_2_(peak oxygen uptake), basal metabolic rate)Glycemic control (fasting glucose, insulin plasma levels, insulin resistance);Lipid profiles (total, LDL, and HDL-cholesterol cholesterol and triglyceride levels)Gut microbiota composition and diversity;Plasma LPS concentration;Inflammatory cell signaling in peripheral blood mononuclear cells (PBMC):NF-κB; toll like receptor (TLR) 2 e 4, TIR-domain-containing adapter-inducing interferon-β (TRIF), inhibitory-κB kinase (IKK)i/ε, e myeloid differentiation primary response 88 (MyD88);Plasma LPS and PBMC inflammatory response to LPS;Inflammatory/anti-inflammatory markers:C-reactive protein level, tumor necrosis factor(TNF)-α, interleukin (IL)1β, IL-4, IL-6, IL-10, HSP72, adiponectin and leptin);Flow mediated dilation (FMD).

### Recruitment and participant timeline

The recruitment period for this study will be from January 2024 to December 2025. Participants will be invited to participate in the study through announcements in newspapers, electronic media, and social media. Figure 2 illustrates the study design.

**Figure 2 F2:**
[figure not shown]
Flow of the study design.

### Adherence

Adherence to an exercise program was defined as meeting > 80% of the recommended or prescribed exercise doses. Any participant who demonstrates training protocol adherence of 80%, or attends more than 36 sessions, will be considered adherent. Participants will be classified as non-adherent or partially adherent if their adherence is < 80%.

### Statistical considerations

To assess the effect of exercise on plasma HSP levels between the groups post-intervention, we assumed 80% power, 5% significance level, and an effect size (Cohen’s F) of 0.4. We estimated a dropout rate of 10%, and the calculated total number of patients was 22 in each group.^
24
^

The randomly assigned participants’ data will be analyzed according to the intention-to-treat principle as the primary choice and the per-protocol principle, with treatment, time, and treatment-time interaction registered as fixed effects. We will qualitatively document the reasons for, and details of, each withdrawal case. The normality of the data will be tested using the Shapiro-Wilk test. Mean and standard deviation will be used to describe parametric continuous variables, with median and interquartile range for non-parametric variables, and absolute and relative frequencies for categorical variables. Analysis of variance (ANOVA) will be used to compare the final outcomes. Treatment effects (group, time, and group interaction) will be estimated using Generalized Estimation Equations (GEE), followed by the Bonferroni post-hoc test (P < 0.05). Multiple linear regression analysis (backward method) will be performed to investigate the impact of routine pharmacotherapy, sex, and age on the primary and secondary outcomes. SPSS Professional software (version 20.0; IBM Corp., Armonk, New York, United States) will be used for all analyses.

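### The stated 22 per group is the no-dropout requirement for the stated inputs; after the assumed 10% dropout, power is about 77%, not 80%

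*Protocol article*

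**What the plan says.** The Statistical considerations section of the protocol article gives the calculation in two sentences. The target is described as "To assess the effect of exercise on plasma HSP levels between the groups post-intervention". The inputs are "we assumed 80% power, 5% significance level, and an effect size" measure, specified as "an effect size (Cohen’s F) of 0.4". The result follows in the same sentence as the dropout assumption: "We estimated a dropout rate of 10%, and the calculated total number of patients was 22 in each group".

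Three other places fix the remaining inputs:

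- The Interventions section names three groups: control, resistance training and heat therapy.
- The Allocation section provides for equal allocation and runs randomisation up to the calculated total. The number randomised is therefore 3 × 22 = 66; no larger enrolment figure appears anywhere.
- Later in Statistical considerations, the test that matches Cohen's f is named: "Analysis of variance (ANOVA) will be used to compare the final outcomes".

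**The concern.** Because the dropout assumption and the group size share a sentence, a reader takes 22 per group to be the figure after an allowance for 10% loss, with 80% power remaining among completers. But 22 is also what the other inputs give before any allowance is made. If so, the dropout was named but not applied, and the power claim and the sample size cannot both hold under the paper's own assumption.

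At stake is the accuracy of a headline design figure for the trial's primary comparison. A null result would be read against a power slightly higher than the design delivers at the expected loss. The estimand, the risk of bias and the validity of the analysis are not affected.

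**Working it through.** **Inputs.** Three groups (Interventions); equal allocation, 66 randomised (Allocation); Cohen's f = 0.4, alpha = 0.05, power 80%, dropout 10% (Statistical considerations). The article does not name the test used for sizing. A Cohen's f for a between-group comparison at one time point implies a one-way fixed-effects ANOVA, so that is the model used here.

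**Formula.** Power = P(F′ > F_crit), where F_crit is the 95th percentile of the central F distribution with 2 and N − 3 degrees of freedom. F′ is noncentral F with the same degrees of freedom and noncentrality λ = N·f² = 0.16·N.

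**Step 1: the plan's own figure, no dropout.**

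| Analysed per group | N | λ = 0.16·N | Power |
|---|---|---|---|
| 20 | 60 | 9.60 | 77.6% |
| 21 | 63 | 10.08 | 79.8% |
| 22 | 66 | 10.56 | 81.8% |

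The smallest equal group size reaching 80% is 22. The stated figure is reproduced exactly, with dropout left out.

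**Step 2: apply the stated dropout to the stated size.** 66 × 0.9 = 59.4 completers.

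| Completers | λ | Power |
|---|---|---|
| 59 | 9.44 | 76.8% |
| 59.4 | 9.50 | 77.1% |
| 60 | 9.60 | 77.6% |

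The shortfall is 80 − 77.6 = 2.4 to 80 − 76.8 = 3.2 percentage points.

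**Step 3: size that would hold 80% after 10% dropout, unadjusted.** Starting from 22 per group, 22/0.9 = 24.4, so 25 per group (75 in total). Starting from the smallest total without a balance restriction, N = 64 (80.5%), 64/0.9 = 71.1, so 72 in total or 24 per group. Accepting 21 per group as near enough to 80% gives 21/0.9 = 23.3, again 24. The fair reference range is 24 to 25.

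**Step 4: can 22 be reached with dropout included?** Variants tried on the stated f, with and without the allowance:

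- Chi-square approximation: 21 before dropout, 24 after.
- Two groups: 26 before, 29 after.
- Four groups: 19 before dropout, but the trial has three.
- Alpha 0.10: 17 before, 19 after.
- Repeated-measures between-group test, two time points, correlation 0.7, λ = N·f²·2/(1 + 0.7): 19 before, 19/0.9 = 21.1, so **22** after.
- Baseline-adjusted ANCOVA, correlation 0.3, λ = N·f²/(1 − 0.3²): 20 before; **22** if inflated as 20 × 1.1, 23 if inflated as 20/0.9.
- One-sided two-group normal approximation: 20 before, **22** as 20 × 1.1.

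Each route to 22 with dropout needs an input that the article does not state: a correlation, or a one-sided two-group test.

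**The case against.** The strongest reply is that the sizing model is inferred. The article cites a source for the calculation that is not at hand. The same section plans a model with treatment, time and their interaction, and outcomes are measured at two times. A repeated-measures calculation with correlation 0.7 does give 22 after dropout. This stands to the extent that the finding must be conditional on the one-way model, and the fix must leave room for another model. It does not remove the finding. No correlation is stated, the comparison is described as post-intervention between groups, and the match with the one-way no-dropout size is exact.

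A second reply is that the planned analysis may recover the loss. Adjusting for baseline with a correlation of 0.3 would give 81.5% power at 60 completers and 80.8% at 59. A change-type contrast from the GEE would reach 80% at about 60 completers if the correlation were somewhat above 0.5. These correlations are assumptions, because the article gives none. So the shortfall is shown for the unadjusted comparison of final values, not for every analysis the section plans. The intention-to-treat principle does not itself restore the loss: outcomes are measured only at baseline and week 12, so a participant who leaves has no week-12 value.

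A third reply is that the deficit is small and arises only if the full 10% is lost. That is correct. With losses between none and 10%, power lies between about 82% and 77%.

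**Conclusion.** The point holds as a modest correction of a stated figure. Under the one-way ANOVA that the stated inputs imply, 22 per group is the size before dropout. Power for the omnibus F test is about 82% with nobody lost and about 77% (76.8% to 77.6%) at the assumed 10% loss. The result assumes f = 0.4 as stated, roughly equal losses across groups and no use of baseline values.

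Three stronger readings are tempting, and the article does not support them:

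- *The trial never had 80% power.* It has about 82% if retention is complete, and a baseline-adjusted analysis could reach 80% after dropout.
- *The trial must enrol 25 per group.* The reference figure is 24 to 25 depending on rounding, and it matters only if an unadjusted 80% after dropout is to be kept. Restating the power is enough.
- *The pairwise comparisons are underpowered by a known amount.* The article claims no pairwise power and does not say how many comparisons the Bonferroni correction covers. Any figure depends on that number and on the pattern of means. Assuming three comparisons and 20 per arm, power is about 58% for either active group against control if both active groups share one mean. With evenly spread means it is about 72% for the extreme pair but only about 18% for an adjacent pair. No single figure can be drawn from the article.

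**What to change.** Replace the sample size result with a sentence such as:

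> *Twenty-two participants per group (66 randomised) give about 82% power for the omnibus F test with no dropout, and about 77% with the expected 10% dropout.*

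If a repeated-measures or baseline-adjusted model was in fact used for sizing, name that model and its assumed correlation instead, so that 22 per group can be reproduced with the dropout allowance included. If the sponsor prefers to keep an unadjusted 80% after 10% loss, the corresponding size is 24 to 25 per group, that is 6 to 9 more participants in total (72 − 66 or 75 − 66).

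Do not add a pairwise power figure unless the number of comparisons and the assumed pattern of means are given with it.

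The cost is one sentence and a slightly less favourable stated power. No additional participants, assessments or changes to the analysis are required.
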